## Methods/Design

A matched pairs randomised trial will be conducted using an activity based day camp model[30] to evaluate the efficacy of CIMT compared to BIM training in children with congenital hemiplegia aged 5 to 16 years.

The specific hypotheses to be tested are:-

1. CIMT will reduce activity limitations and participation restrictions to a greater extent than BIM training in children with hemiplegia.

2. CIMT will result in greater use-dependent brain reorganisation compared to BIM training and this cortical plasticity will be retained for longer periods.

3. CIMT will result in greater enhancement of participation in school and community roles.

4. CIMT will result in greater improvements in QOL.

These hypotheses will address the following specific aims:-

1. Upper limb rehabilitation consumes a great deal of time and is costly, and the effects may be short lived. CIMT is a novel upper limb training where the unimpaired arm is constrained in a "glove like splint" while the impaired hemiplegic arm is intensively trained. This study will determine which training approach has the greatest impact on activity limitations and how long that effect is retained.

2. If one approach results in greater enhancement and retention of cortical reorganisation then this will guide clinical practice with implications for other patients (Traumatic Brain Injury TBI, stroke). An understanding of the nature and timing of the brain lesion may indicate which children respond better.

3. If a training program enhances community participation and improves QOL this will have a profound impact on educational opportunities and vocational roles.

Assessments will be performed at baseline prior to the camp and then at three weeks following completion of the camp. Further follow-up will be performed at 26 and 52 weeks following intervention to determine retention of effects. The experimental design and outcome measures are depicted in Figure 1.

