### Sample size

According to CONSORT guidelines the primary basis for sample size calculation is adequate power for the comparison between the functional effects of CIMT and BIM training at 3 weeks post intervention. Based on data from a previous study[33], a mean difference of 7 percentage points was proposed or 10% of the anticipated control group mean at baseline on the Melbourne Assessment of Unilateral Upper Limb Function[34] as the minimum difference that is likely to have substantial clinical importance. Our pilot data in a study of UL training with and without intramuscular BoNT-A injections yielded standard deviation of changes of 7.6 and 9.6 units in the two groups. Based on a t-test comparison of changes using a SD of 9 units for both groups, significance (alpha) level of 0.05, and 80% power, we require 26 participants in each group (total sample of 52).

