**Games**			
a) Parachute		Grasp, shoulder flexion, extension, adduction, elbow and wrist extension, supination, throw and catch	Symmetric and asymmetric movements, stabilisation, grasp, shoulder flexion, extension, adduction, elbow and wrist extension, supination
b) Sports			
**Debriefing**	0.5 hour	Group discussion about day	Group discussion about day

Children will return to their regular therapy programs at the completion of the 2-week program. Documentation of concurrent therapy programs (ongoing, additional therapy or interventions, change in spasticity, medications or lower limb interventions) will be recorded at each follow up assessment as these would not be able to be controlled over a 12 month period.

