### Comparison to Typically developing children

Fifty-two typically developing peers ("buddies") matched with the study participants according to age, gender and classroom that they attend will be invited to participate. Typically developing children in this 'bring a buddy" system will be assessed at baseline, 26 and 52 weeks to provide a reference for participation in home, school and community life and QOL. At study entry the typically developing age and gender matched controls "the Buddies" will meet the following criteria:

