### Analyses

All assessment forms will be developed using scannable Teleforms (Teleform, 2005). Forms will be entered, scanned and visually checked by staff trained in use of the software. Data will be transferred electronically into Microsoft Access 1997. Analyses will be on an intention-to-treat basis using STATA 10. Data from each outcome measure will be summarised for each treatment group and descriptive statistics (frequencies, means, medians, 95% confidence intervals) calculated dependent on data distribution. We anticipate that groups will be similar on baseline measures due to the matched pairs design. Initially between group differences will be evaluated at the three follow-up assessment points using independent t-tests or Wilcoxon rank sum test. Within group changes between baseline and the follow-up assessments for continuous variables will be evaluated using paired t-tests or Wilcoxon matched-pairs sign rank test. A significance level of 0.05 will be used.

For the TMS data Student's paired t-test will be used for analysis of the difference between pre and each post intervention (3 and 26 weeks) mean MT and MEP ratios. This will be performed in each group for the impaired side and the unimpaired side.

To determine the intra-rater reliability of our trained occupational therapist rater on the MUUL, intraclass correlation coefficients will be calculated (3.1) with 95% confidence intervals from total MUUL percentage scores[101]. The standard error of measurement (SEM = SD × √(1-ICC)) and the smallest detectible difference (SDD = SEM × 1.96 × √2) will be calculated[102].

Post hoc analyses will be undertaken to investigate clinical characteristics of children who have a greater response to either intervention.

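### The within-arm tests against baseline, run at the same 0.05 level as the randomised comparison, cannot show that either programme works or that its effect lasts

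*Protocol article*

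**What the plan says.** The Analyses section of the protocol article opens its inferential plan with the randomised comparison: "Initially between group differences will be evaluated at the three follow-up assessment points using independent t-tests or Wilcoxon rank sum test". The next sentence adds the within-arm tests: "Within group changes between baseline and the follow-up assessments for continuous variables will be evaluated using paired t-tests or Wilcoxon matched-pairs sign rank test". One threshold then covers both: "A significance level of 0.05 will be used". Nothing marks the within-arm tests as descriptive.

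The surrounding design is as follows.

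- **Purpose of follow-up.** Under Methods/Design, the 26- and 52-week visits serve to look at retention, and the first aim reads: "This study will determine which training approach has the greatest impact on activity limitations and how long that effect is retained".
- **Arms.** Both are active (Abstract; Randomisation). There is one assessment before the camp and no untreated group with hemiplegia.
- **Children.** Aged 5 to 16 (Inclusion criteria), assessed at baseline and at three follow-ups.
- **After the camp.** In the text after Table 1: "Children will return to their regular therapy programs at the completion of the 2-week program". Other therapy is logged at each follow-up, and the authors acknowledge that they cannot control it over 12 months.
- **Typically developing buddies.** They "will be assessed at baseline, 26 and 52 weeks to provide a reference for participation in home, school and community life and QOL". They complete the CAPE, LIFE-H and Kidscreen only.

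**The concern.** A paired test against baseline asks whether the mean change differs from zero. It does not ask why. Over 26 or 52 weeks a child aged 5 to 16 grows, becomes familiar with the tests and goes back to regular therapy. Each of these can move a score without any lasting effect of a two-week camp, and in a within-arm test they cannot be separated from it.

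What is at stake is the conclusion. If both arms improve on baseline and do not differ from each other, it would be easy to conclude that both programmes work and that both effects last. The design cannot support that. If one arm crosses 0.05 and the other does not, the pair of results can look like a difference between the programmes when there is none. The comparison of CIMT with BIM training is itself not at risk from drift that the two arms share.

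**Working it through.** **Inputs.** From the Sample size section: "a mean difference of 7 percentage points was proposed or 10% of the anticipated control group mean at baseline", that is, 7 MUUL points; and "using a SD of 9 units for both groups, significance (alpha) level of 0.05, and 80% power, we require 26 participants in each group". The pilot SDs of change given there are 7.6 and 9.6. Drift unrelated to the camp is not given anywhere. It is assumed to be 1 to 5 MUUL points, with a training effect of zero.

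**1. The plan's own figure.** Two-sided normal approximation:

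n per arm = 2 × (1.960 + 0.842)² × 9² / 7² = 2 × 7.85 × 81 / 49 ≈ 25.95, so 26.

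This reproduces the stated 26 per arm (power 0.801). The t-based calculation gives 26.9, with power 0.785 at 26, which is close enough. The sample size was set for the between-arm comparison.

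**2. Smallest mean gain that is significant within an arm.**

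Critical gain = t(0.975, 25) × SD / √26

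- SD 9: 2.060 × 9 / 5.099 = 2.060 × 1.765 = 3.64
- SD 7.6: 3.07
- SD 9.6: 3.88

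At SD 9 this is about half of the 7 points set as the important difference between groups (3.64 / 7 = 0.52).

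**3. Chance that an arm with no training effect is significant.** Noncentral t with 25 degrees of freedom and noncentrality = drift / (SD / √26). At SD 9 and 3 points, noncentrality is 3 / 1.765 = 1.70.

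| Assumed drift (points) | SD 7.6 | SD 9 | SD 9.6 |
|---|---|---|---|
| 0 | 5% | 5% | 5% |
| 1 | 9.9% | 8.5% | 8.0% |
| 2 | 25% | 19% | 18% |
| 3 | 49% | 37% | 33.5% |
| 4 | 73% | 59% | 53% |
| 5 | 90% | 78% | 72% |

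**4. The same drift in both arms, no training effect in either.** 20,000 simulated trials, 26 per arm, SD 9:

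| Drift (points) | Between-arm test significant | At least one arm significant | Exactly one arm significant |
|---|---|---|---|
| 0 | 5.1% | 10% | 9% |
| 2 | 4.8% | 35% | 31% |
| 3 | 5.2% | 61% | 46% |
| 4 | 4.8% | 83% | 48% |
| 5 | 4.8% | 95% | 35% |

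The randomised contrast keeps its error rate at every drift because the drift cancels. The within-arm tests do not. The last column shows how often comparing one arm's p-value with the other's would suggest a difference that does not exist.

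**The case against.** The strongest reply is that the trial is a head-to-head comparison and is planned as one. The between-arm tests come first and cover all three follow-ups, the hypotheses set CIMT against BIM training, and the sample size rests on a between-arm t-test of changes. Omitting an untreated arm is a legitimate choice for that question. All of this stands. A reader might infer that effect and retention are judged by before-after tests alone; the Analyses section rules that out.

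Several other stronger readings also fail.

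- **That a within-arm gain will be reported as a lasting training effect.** The article never says so. The tests permit that reading, and the plan does nothing to close it off.
- **That the first aim asks how long each programme's effect lasts.** Its wording is comparative.
- **That the 3.6-point threshold is alarming beside the 8.9% smallest detectable difference cited for the MUUL.** That figure is for an individual child, whereas 3.6 is a group mean. The two are not comparable.
- **That season explains a 52-week gain.** That visit falls at about the same time of year as baseline.
- **That regular therapy is in effect the comparator.** The Background describes the bimanual approach as historical and current management as task-oriented, functional or motor-learning.
- **That the buddies supply the missing control.** They are typically developing and contribute nothing on the MUUL or other hand-function measures.

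The drift is also assumed, and the MUUL is a criterion-referenced percentage score that may change little with age. With no drift the within-arm test has its nominal 5%.

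Finally, the between-arm difference cannot say how long each effect lasts: it is zero if both arms keep everything and zero if both lose everything. That is correct, and it limits what the trial can conclude under any analysis.

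**Conclusion.** The point holds in a limited form. The randomised comparison is sound against drift common to both arms. The within-arm tests, fixed at the same 0.05 level and not labelled descriptive, cannot establish that either programme works or that its effect is retained.

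The threshold of about 3.6 MUUL points (3.1 to 3.9 over the pilot SDs) follows from the protocol's own figures. The 8.5% to 78% range does not: it rests on an assumed drift of 1 to 5 points, a zero training effect, SD 9, complete follow-up of 26 per arm and roughly normal changes. It shows how sensitive the within-arm tests are to drift. It does not predict the size of the drift in this trial. The remedy concerns the role of a stated analysis; the design and the sample size are unaffected.

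**What to change.** 1. Report within-arm changes from baseline descriptively, with 95% confidence intervals and with no claim of efficacy or retention attached.
2. Base conclusions on effect and retention on the between-arm difference in change from baseline at 3, 26 and 52 weeks.
3. Describe what is compared at 26 and 52 weeks as camp followed by regular therapy, and state that the contrast shows relative retention only.
4. Where useful, show the buddies' change on the CAPE, LIFE-H and Kidscreen beside each arm's change at 26 and 52 weeks, as a descriptive reference and not as a control.

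This uses data already being collected and leaves 26 per arm unchanged; only the analysis text and the wording of conclusions change. The price is that the trial gives up any stand-alone claim that either programme works or lasts. In particular, improvement in both arms without a difference between them could not be reported as evidence that both are effective.

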## Discussion

This paper presents the background and design for a matched pairs randomised trial comparing CIMT and BIM training for children with congenital hemiplegia. This study is the first to directly compare the two approaches and will be the largest study of either approach to date. Furthermore, we will be evaluating the outcomes of the intervention program across all domains of the ICF using valid and reliable measurement tools. It is anticipated that the results of this study will be disseminated widely through peer reviewed journals and international academic conferences.

## Abbreviations

CP: Cerebral palsy; CIMT: Constraint induced movement therapy; BIM training: Bimanual training; UL: Upper limb; MUUL: Melbourne Assessment of Unilateral Upper Limb Function; AHA: Assisting Hand Assessment; JTTHF: Jebsen Taylor Test of Hand Function; COPM: Canadian Occupational Performance Measure; LIFE-H: Assessment of Life Habits; CAPE: Children's Assessment of Participation and Enjoyment; SFA: School Function Assessment; CHIEF: Craig Hospital Inventory of Environmental Factors; CPQOL-Child: Cerebral Palsy Quality of Life Questionnaire for Children; TMS: Transcranial Magnetic Stimulation; fMRI: Functional Magnetic Resonance Imaging; ICF: International Classification of Functioning, Disability and Health.
